# Prospective, observational study to assess the performance of CAA measurement as a diagnostic tool for the detection of *Schistosoma haematobium* infections in pregnant women and their child in Lambaréné, Gabon: study protocol of the freeBILy clinical trial in Gabon

**DOI:** 10.1186/s12879-020-05445-1

**Published:** 2020-09-29

**Keywords:** Schistosomiasis, *Schistosoma haematobium*, Clinical trial, UCP-LF CAA, *Schistosoma* circulating antigen, Pregnancy, Infant, Diagnostic test, Praziquantel, Gabon

## Abstract

**Background:**

*Schistosoma* antigen detection in urine is a valuable diagnostic approach for schistosomiasis control programmes because of the higher sensitivity compared to parasitological methods and preferred sampling of urine over stool. Highly accurate diagnostics are important in low *Schistosoma* transmission areas. Pregnant women and young children could particularly benefit from antigen testing as praziquantel (PZQ) can be given to only confirmed *Schistosoma* cases. This prevents the unborn baby from unnecessary exposure to PZQ. We present here the protocol of a diagnostic study that forms part of the freeBILy project. The aim is to evaluate the accuracy of circulating anodic antigen (CAA) detection for diagnosis of *Schistosoma haematobium* infections in pregnant women and to validate CAA as an endpoint measure for anti-*Schistosoma* drug efficacy. The study will also investigate *Schistosoma* infections in infants.

**Methods:**

A set of three interlinked prospective, observational studies is conducted in Gabon. The upconverting phosphor lateral flow (UCP-LF) CAA test is the index diagnostic test that will be evaluated. The core trial, sub-study A, comprehensively evaluates the accuracy of the UCP-LF CAA urine test against a set of other *Schistosoma* diagnostics in a cross-sectional trial design. Women positive for *S. haematobium* will proceed with sub-study B and will be randomised to receive PZQ treatment immediately or after delivery followed by weekly sample collection. This approach includes comparative monitoring of CAA levels following PZQ intake and will also contribute further data for safety of PZQ administration during pregnancy. Sub-study C is a longitudinal study to determine the incidence of *S. haematobium* infection as well as the age for first infection in life-time.

**Discussion:**

The freeBILy trial in Gabon will generate a comprehensive set of data on the accuracy of the UCP-LF CAA test for the detection of *S. haematobium* infection in pregnant women and newborn babies and for the use of CAA as a marker to determine PZQ efficacy. Furthermore, incidence of *Schistosoma* infection in infants will be reported. Using the ultrasensitive diagnostics, this information will be highly relevant for *Schistosoma* prevalence monitoring by national control programs as well as for the development of medicaments and vaccines.

**Trial registration:**

The registration number of this study is NCT03779347 (clinicaltrials.gov, date of registration: 19 December 2018).

## Background

Schistosomiasis is one of most widespread human parasitic diseases worldwide [1, 2]. Infections with blood flukes of the genus *Schistosoma* are endemic in 74 countries with more than 230 million individuals being infected and 90% of infections are occurring in sub-Saharan Africa [3]. *Schistosoma haematobium* is highly prevalent in Africa [4] resulting in chronic morbidities, particularly affecting urogenital organs. Women in child-bearing age suffer two-fold from *Schistosoma* infections: directly from immune-pathological effects induced by worm infection, and indirectly from potential adverse birth outcomes during pregnancy [5].

Currently, there is no vaccine available against schistosomiasis and control is based on a single drug - praziquantel (PZQ) for chemotherapy and prevention. The 2012 WHO roadmap on neglected tropical diseases calling for schistosomiasis elimination initiated a tremendous increase in PZQ deployment [6]. This fuelled the ever-growing concern of emergence of PZQ resistant *Schistosoma*, particularly since schistosomes with reduced susceptibility have been identified sporadically in sub-Saharan Africa [7–10]. However, drug efficacy outcomes largely depend on the accuracy of the surrogate endpoint measures that reflect treatment effects in clinical trials [11]. Clinical evaluation of PZQ efficacy, of new PZQ formulations (e.g. paediatric) [12] or of new drug candidates relies on reliable diagnostic instruments to correctly judge a drug’s potency to kill *Schistosoma* infections in humans. Egg microscopy is still the reference standard widely used in schistosomiasis diagnosis but the methodology lacks sensitivity and cannot precisely measure drug efficacy due to huge variation in egg counts intrinsically associated with egg excretion that varies from day-to-day and occurs in clusters in stool [13–17]. Egg reduction rates vary considerably in a study cohort necessitating a huge sample size in clinical trials to be able to identify significant differences between the investigational product and the control. Furthermore, available PZQ efficacy data may be limited [18, 19].

Pregnant women and their infants are two vulnerable population groups, particularly in sub-Saharan Africa, who - amongst other infectious agents - are heavily exposed to *Schistosoma* infections. Infants were thought not to be exposed enough to get infected in their first months of life, however meanwhile high infection rates in infants aged as young as 3 months have been demonstrated [20]. *Schistosoma* infection causes nutritional and hematologic deficits and overt pathology caused by chronic inflammation to eggs trapped in the bladder and urogenital tissues and can lead to granulomatosis and progress to fibrosis and cancer at the late stage. Approximately 20 million women are suffering from female genital schistosomiasis (FGS) which is caused by embolized eggs in tissues of the uterus, cervix and the lower genital tract associated with bleeding and pain. FGS is a significant risk factor for HIV infection [21, 22].

Detrimental effects of maternal schistosomiasis during pregnancy on the foetus may lead to poor birth outcomes including low birth weight, preterm delivery and maternal anaemia [5, 23, 24]. Schistosomiasis is a large contributor to anaemia and undernutrition and is per se unfavourable for the developing foetus. In 2002, the WHO recommended that all pregnant women positive for *Schistosoma* should be treated with PZQ either individually or as part of mass drug administration (MDA) programs during the second and third trimester [25, 26]. Adoption of the recommendation and implementation by national disease control programs was however delayed in most African countries, due to the side-effects of PZQ and the lack of safety data in pregnant women and unborn babies. First results from randomised controlled trials with PZQ in pregnancy meanwhile have provided evidence for the safety of PZQ also in newborns [27, 28]. Nonetheless, pregnant women, unborn babies and newborns are vulnerable populations and there is a reluctancy to include them in PZQ (mass) treatment campaigns as this would imply unnecessary exposure to PZQ (even of pregnant women and infants that are not infected). In addition, logistical and financial obstacles have delayed implementation of PZQ preventive chemotherapy in pregnant women at country levels. Accordingly, innovative patient-centred approaches, combining accurate schistosomiasis diagnosis and targeted treatment during pregnancy, are needed to control schistosomiasis in this population.

### Rationale for the study

In Gabon, *S. haematobium* is the major prevalent *Schistosoma* species and *S. intercalatum* [29] is present only at a minimal level. According to the recommended WHO strategy, in 2015 a total of 343.554 individuals would have required preventive schistosomiasis treatment in Gabon alone [30]. Despite being an upper middle-income country [31], there is no effective national control program for schistosomiasis established in Gabon, but rather the National Program for neglected tropical diseases (NTD) which includes schistosomiasis and other neglected diseases. A recently published study indicated that approximately 10% of the pregnant women living in Lambaréné and Fougamou vicinities tested positive for *S. haematobium* infection with increased odds (OR1.7, 95% CI 1.03–2.82) for low birth weights of the newborns [32, 33]. As it is true for most of the observational and interventional studies on schistosomiasis, the power of the study was weakened due to the low sensitivity of the reference schistosomiasis diagnosis applied (egg microscopy), and one might assume that a considerable proportion in the control group were misclassified as negative.

Diagnostic tests that are highly sensitive and specific are essential for the detection of *Schistosoma* infections and are urgently needed in a variety of applications such as a test-and-treat strategy to control schistosomiasis in pregnancy and as tools to determine efficacy of new interventions in clinical trials. Detection of *Schistosoma* circulating antigens is becoming an important *Schistosoma* diagnostic strategy. Circulating anodic antigen (CAA) and circulating cathodic antigen (CCA) are constantly released by schistosomes into the host circulation and day to day fluctuation of CAA in serum is relatively little [34]. Furthermore, CAA levels are correlating with the number of worms [35, 36]. As CAA and CCA have been shown to clear within a few days or weeks after PZQ treatment [18, 34, 37], assays measuring antigen levels are promising techniques to more accurately assess drug efficacy. Particularly, the detection of circulating anodic antigen (CAA) by the up-converting phosphor-based lateral flow (UCP-LF) technology has proven to be a highly sensitive and specific diagnostic tool for schistosomiasis [37–39]. The high sensitivity and specificity of the UCP-LF CAA test is warranted by the uniqueness of the antigen to the *Schistosoma* genus, in combination with specific, high affinity monoclonal antibodies, a carbohydrate specific sample pre-treatment step and a unique background free reporter technology [37, 40, 41].

The overall aim of this study is to evaluate the accuracy of the UCP-LF CAA urine test for the detection of *S. haematobium* infections in pregnant women and to validate CAA as an endpoint measure for PZQ efficacy. This study is part of the *Fast and Reliable Easy-to-Use Diagnostics for Eliminating Bilharzia in Young Children and Mothers* (freeBILy) project which aims to thoroughly evaluate the use of CCA and CAA antigen tests for the diagnosis of *Schistosoma* infections in pregnant women and their newborns [42]. The freeBILy project is complemented by an additional trial performed in Madagascar that investigates a CCA-based test-and-treat strategy integrated into routine maternal and child primary health care programmes.

## Methods

### Study design

The freeBILy Gabon-study consists of a set of 3 interlinked prospective, observational sub-studies (A-C), each targeted to assess a specific objective (see Fig. 1 for a schematic trial design, procedures and stages).

**Fig. 1 Fig1:**
[figure not shown]
freeBILy-GABON study outline

**Sub-study A** is a prospective, cross-sectional, observational study conducted in 1000 pregnant women in Lambaréné and surroundings to determine the sensitivity and specificity of the UCP-LF CAA test (index test) for the detection of *S. haematobium* infections in urine samples. Sampling will include standardized urine collection on 3 consecutive days for *S. haematobium* detection by egg microscopy and UCP-LF CAA testing; qPCR and POC-CCA will be done on one urine sample. To control for concomitant parasite infections one stool sample (within the 3 days of urine sampling) will be collected to screen for *S. intercalatum* and soil-transmitted helminths infections, as well as one blood sample will be taken for filaria and *Plasmodia* spp. detection. The blood sample will also be used to measure anti-*Schistosoma* antibodies and to provide blood cell counts and haemoglobin levels. The primary objective of sub-study A is to compare the UCP-LF CAA urine test against a composite diagnostic reference including egg microscopy, qPCR, and serology in order to determine UCP-LF CAA test performance. Sub-study A will allow to identify participants for sub-study B.

**Sub-study B** is an observational, follow-up study of at least 100 pregnant women identified in sub-study A as being infected with *S. haematobium* (by egg microscopy and/or urine UCP-LF CAA test). *Schistosoma*-infected women will be randomised 3:1 (75:25) for immediate PZQ treatment during the pregnancy (single dose of 40 mg/kg) or delayed PZQ treatment after delivery (control group). The control group will not be treated during pregnancy (to monitor “natural” CAA level fluctuation in a participant if not treated), but 6 months after delivery. The primary objective is to determine the kinetics of CAA after treatment during pregnancy compared to the control group. The control group serves also as a safety control of PZQ administration to pregnant women and exposure of their offspring (s). Therefore, both groups (treatment and control) will be actively followed-up and urine will be collected on day 2, day 4 and day 6 after PZQ treatment and then once a week until both egg microscopy as well UCP-LF CAA assay become negative but no longer than 6 weeks after PZQ treatment. The secondary objective is to collect data on safety of PZQ during pregnancy. For details on the safety investigation, see below (treatment, adverse events and safety assessment).

**Sub-study C** will follow up infants born to mothers included in sub-study A and their mothers for a maximum of 24 months (*N* = 200). This is an observational, longitudinal study with the primary objective to determine the incidence of *S. haematobium* infection and age of first *S. haematobium* infection in infants. Therefore, after delivery, mother and her infant will be asked to provide urine every 3 months until the UCP-LF CAA test becomes positive for *S. haematobium* in the infant. Children who test *S. haematobium* positive will be treated with praziquantel according to Gabonese national treatment guidelines.

In addition, a customized questionnaire addressing the knowledge, attitude and practice (KAP) of schistosomiasis of mothers and infants will be asked. Health-related quality of life (HRQoL) will also be measured by using a standardized tool: this will allow filling a wide literature gap, where only very few studies have attempted to measure HRQoL in schistosomiasis endemic areas [43]. To our knowledge, this study will be the first one collecting information on HRQoL among pregnant women in areas endemic of schistosomiasis and of other parasitic infections such as malaria.

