### Diagnostics

#### Investigational product: UCP-LF CAA test

The index test is the UCP-LF strip test detecting and quantifying CAA levels. LF strips can be analysed with POC care readers [47] or, as used in this study, with a multistrip benchtop reader (Upcon; Labrox Oy, Turku, Finland) capable of analysing 20 strips at a time. The UCP-LF CAA test was developed at Leiden University Medical Center (Leiden, The Netherlands) [38, 48]. So far, the tests are produced in-house at LUMC in a batch-wise manner (ca. 2000 tests per batch), fully quality-controlled using standardized reference samples, ensuring specificity and sensitivity. A dry reagent format is available that can be stored and transported at ambient temperature [39]. Here, 417 μl of fresh or stored (− 20 °C) urine will be tested by the UCP-LF CAA urine test following published procedures [48] including a concentration step (centrifugal Amicon Ultra 0.5 mL filters with a 10 kD cut-off; Merck Millipore) after pre-treatment of the urine with 1/6 volume of 12% trichloroacetic acid and (UCAA*hT*417 format) [49]. All measurements will include a set of CAA-spiked standards into a negative urine to determine the threshold of positivity that is set to ≥2 pg/ml.

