### Sample size calculation

Analysis of the UCP-LF CAA (UCAA*hT*417) test performance will be compared against a composite diagnostic reference (i.e. by latent class analysis). Assuming a 10% egg positivity rate in the study population [32], about 1000 pregnant women should be tested to obtain 100 *Schistosoma* positive women. Assuming further a sensitivity of the index test (UCP-LF CAA) between 80 and 100% with 100 infected women, statistical precision (two-sided 95% confidence limit) of ±7.8% will be achieved if a sensitivity of 80% is observed and a lower limit of 96.4% if a sensitivity of 100% is observed. Due to the limited sensitivity of the egg detection test, to estimate the specificity, only study participants negative for reference tests should be included. Furthermore, assuming a true *Schistosoma* prevalence of 20% (based on a conservative estimate of 50% sensitivity of the egg test) and assuming a false positive rate of 20% of the other two reference tests (PCR and UCP-LF antibody test), at least 500 women will enter the naïve estimate of specificity. This will lead to a statistical precision of between ±3.5 and ± 4.3% depending on the observed specificity. For sub-study B, the analysis is based on the assumption of a non-inferiority delta of 0.10, identical probabilities of positivity and negativity at the end of the sub-study B for both tests (UCP-LF CAA and egg microscopy) and a discordance of 12%, with 100 pregnant women, the power will be 80% to show non-inferiority (type 1 error: 2.5% one-sided).

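### Sub-study C ends an infant's sampling at the first positive of up to eight CAA tests, so accumulated false positives inflate the incidence of infection unless specificity is close to perfect

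*Protocol article*

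**What the plan says.** The protocol article (Methods, Study design, Sub-study C) gives sub-study C the "primary objective to determine the incidence of *S. haematobium* infection and age of first *S. haematobium* infection in infants". Infants (N = 200) are followed "and their mothers for a maximum of 24 months". From this objective it derives the sampling rule: "mother and her infant will be asked to provide urine every 3 months until the UCP-LF CAA test becomes positive" in the infant. It continues: "Children who test *S. haematobium* positive will be treated with praziquantel according to Gabonese national treatment guidelines". The article mentions no second result before an infant counts as infected.

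The section on the UCP-LF CAA test gives one cut-off, "to determine the threshold of positivity that is set to ≥2 pg/ml", and allows the assay to be run on fresh or frozen urine.

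In sub-study A, by contrast, the same test is judged in women against a composite of egg microscopy, qPCR and serology, with urine taken on three consecutive days. On specificity, the sample size section says that "at least 500 women will enter the naïve estimate of specificity" and adds: "This will lead to a statistical precision of between ±3.5 and ± 4.3% depending on the observed specificity". It gives no planning figure for sub-study C.

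The Discussion part of the abstract announces accuracy data for "infection in pregnant women and newborn babies". The aims in the abstract's Background and in the Rationale confine the accuracy evaluation to pregnant women.

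**The concern.** A specificity that looks excellent in a single cross-sectional test can be poor when the test is repeated up to eight times and the first positive settles the outcome. An uninfected infant has a fresh chance of a false positive at each visit. A falsely flagged infant also leaves the sampling schedule, so a later true infection in that infant is not recorded as such.

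Both primary outcomes of sub-study C depend on that first positive: the incidence of infection and the age at which it occurs. If true incidence is low, much of what is reported as infant infection could be test error. The study's own estimate of specificity comes from pregnant women and need not carry over to infants.

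**Working it through.** **The plan's own figure.** The number of women for specificity is 1000 × 0.80 uninfected × 0.80 × 0.80 negative on the two other reference tests = 512, which agrees with at least 500. The half-width is 1.96·√(p(1−p)/n).
- n = 500: p = 0.80 gives 3.51% and p = 0.60 gives 4.29%.
- n = 512: p = 0.80 gives 3.46% and p = 0.50 gives 4.33%.

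The stated ±3.5 to ±4.3% is reproduced. It states precision, not an expected specificity.

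**Inputs for sub-study C.** From the article: visits every 3 months for 24 months, so 24/3 = 8 tests at most, and 200 infants. Assumed, because the article gives no value: per-test specificity Sp of 95 to 99.5%, true 24-month incidence I of 5 to 30%, independent errors between visits, and sensitivity of 100%.

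**Never-infected infants flagged by 24 months**, 1 − Sp⁸:
- 99.5%: 1 − 0.9607 = 3.9% (8 of 200)
- 99%: 1 − 0.9227 = 7.7% (15)
- 98%: 1 − 0.8508 = 14.9% (30)
- 95%: 1 − 0.6634 = 33.7% (67)

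**True against false first positives.** With constant hazard, the per-visit hazard is h = 1 − (1 − I)^(1/8). An infant still under sampling becomes a true first positive with probability h and a false one with probability (1 − h)(1 − Sp). For I = 10% and Sp = 98%:
- h = 0.01308
- probability of staying negative at one visit: 0.98692 × 0.98 = 0.96718
- expected visits per infant: (1 − 0.90 × 0.8508)/(1 − 0.96718) = 7.14
- true: 200 × 7.14 × 0.01308 = 18.7
- false: 200 × 7.14 × 0.98692 × 0.02 = 28.2

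Expected true/false first positives among 200 infants:

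| Sp | I = 5% | I = 10% | I = 20% | I = 30% |
|---|---|---|---|---|
| 99.5% | 9.8/7.6 | 19.7/7.4 | 39.3/7.0 | 59.0/6.5 |
| 99% | 9.7/15.0 | 19.3/14.6 | 38.7/13.7 | 58.1/12.7 |
| 98% | 9.3/29.0 | 18.7/28.2 | 37.4/26.5 | 56.2/24.7 |
| 95% | 8.4/65.5 | 16.9/63.7 | 33.9/59.9 | 51.1/56.0 |

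For I = 10%, the observed cumulative incidence 1 − (1 − I)·Sp⁸ is 13.5/17.0/23.4/40.3% at Sp = 99.5/99/98/95%.

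**Break-even.** False equals true when Sp = 1 − h/(1 − h). This gives 99.4, 98.7, 97.2 and 95.4% for I = 5, 10, 20 and 30%.

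**Age at first positive, I = 10%, Sp = 99/98/95%.**
- Constant hazard: a true mean of 13.3 months becomes 13.1/13.0/12.5.
- Hazard proportional to the square of the visit number: 18.9 months becomes 16.3/15.2/13.6.

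**Can sub-study A settle specificity closely enough?** Suppose 99% is observed in 500 women. The half-width is 0.87%, so the interval is about 98.13 to 99.87%. Over eight tests that is 1 − 0.9813⁸ = 14.0% down to 1 − 0.9987⁸ = 1.0%, even if specificity in women held for infants.

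**Effect of a second, independent positive**, 1 − (1 − (1 − Sp)²)⁸: 0.08% at Sp = 99%, 0.3% at 98% and 2.0% at 95%.

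**The case against.** - **A condensed article.** It does not literally define an incident case, and it refers visit and sampling details to Additional file 1. A confirmation rule may exist in the full protocol. This stands as a caveat, and if there is such a rule, one sentence resolves the point. The stop rule itself, however, is stated and tied to the primary objective.
- **Unknown inputs.** The article calls the test highly specific without giving a figure, and its Background cites high infection rates in very young infants. With specificity of 99.5% or more and incidence of 10% or more, true positives outnumber false ones. This stands: the size is conditional, although incidence is still inflated.
- **Independence.** It gives the upper bound for the harm. If false positivity were a fixed trait of an infant, the cumulative rate would stay near 1 − Sp, about 2% at 98%. It is also the best case for the remedy, because a persistent false positive would pass a second CAA test.
- **Retesting is possible.** A reader might infer that a false positive can never be discovered. The documents do not support that, since the assay may be run on frozen urine. Ending new collection does not rule out a retest of the positive sample.
- **Age.** A reader might infer that age at first infection is pulled strongly towards the earliest visits. Under constant hazard it is not. Imperfect sensitivity (the article assumes 80 to 100%) and 3-monthly sampling push age upward, so the net direction is not established.
- **Implied specificity.** A reader might infer from the ±3.5 to ±4.3% range that the sponsor expects 80% or less. The range describes precision and does not support that reading.

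**Conclusion.** The point holds in a bounded form. The stated stop rule, with the index test used alone over up to eight visits, inflates the incidence of infant infection unless specificity is close to perfect. Whether false first positives outnumber true ones depends on two quantities that the documents do not give. At 10% true incidence the answer changes at about 98.7% specificity, and at 20% at about 97.2%. These figures assume independent errors, constant hazard and full sensitivity.

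The effect on age at first infection is secondary: 0.2 to 0.3 months at 98 to 99% specificity with constant hazard and 10% incidence, and about 2.6 to 3.7 months if the hazard rises steeply with age (18.9 to 16.3 or 15.2).

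The newborn accuracy claim in the abstract is a smaller matter of wording. It goes beyond the accuracy aims stated elsewhere in the article.

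The sponsor should act, because the change is cheap and affects what sub-study C can conclude.

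**What to change.** 1. Retest the retained pre-treatment urine of every CAA-positive infant visit, by repeat CAA and by qPCR. Do not make egg microscopy a required confirmation, because the sample size section assumes only about 50% sensitivity for it.
2. Report incidence and age at first infection under both definitions, confirmed and single-positive.
3. Add an incidence estimate corrected for specificity and sensitivity, with its uncertainty, over a stated range, because sub-study A estimates accuracy in pregnant women only. The range matters. With full sensitivity, an observed 23.4% corrects through 1 − (1 − 0.234)/Sp⁸ to 17.0% at Sp = 99%, 10.0% at 98% and 2.3% at 97% (0.97⁸ = 0.7837).
4. Limit the abstract's accuracy claim to pregnant women, unless comparator tests are run on infant urine.

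The cost is retesting of positive samples only, provided enough urine is kept, plus a few sentences of endpoint definition. Some true light infections would count only under the single-positive definition. Persistent false positives may survive a repeat CAA test, which is why qPCR is included. New urine after a first positive would add little, since treatment follows and the article says that the antigen clears within days or weeks of it. The treatment rule is untouched.
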